### 2.5. Dissemination Plans

All results will be published in specialized scientific journals. The final data of these studies will be anonymized and will remain accessible after their publication and may justifiably be requested from the main inventors. The results will be made public through the social networks of our institution.

## 3. Discussion

The main objective of the study is to improve the balance of Parkinson’s patients through cognitive rehabilitation. Cognitive rehabilitation in PD has been effective in the rehabilitation of attention and executive functions [44], on the other hand, previous studies relate attention and executive functions with the risk of falls, balance, and gait in PD patients, proposing rehabilitation in these areas as a possible effective therapy [8,45].

All the clinical variables assessed will allow one to identify markers that predict a better outcome of the cognitive intervention on balance rehabilitation, this information will be of great relevance to adjust the intervention to specific profiles of patients with PD who will benefit the most.

Although our study counts with the limitation of a lack of blinding of the participants and some researchers, its design is robust enough to provide with evidence that may support new approaches to stability rehabilitation in PD. Current strategies continue to be based on training in compensatory and signaling strategies, high intensity visual rehabilitation, and exercise such as dance, Tai-Chi, and Yoga [46]. Other studies use virtual reality as part of therapy although there is still no evidence on its efficacy [47]. The use of virtual reality implies the transfer of patients to a specialized center and continuous supervision. Our study proposes a home-based protocol that can improve the quality of life of Parkinson’s patients even from their own home avoiding the current pandemic limitations on medical care.

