### 2.1. Study Design and Participants

The participants will be recruited in PD outpatient’s clinic of the Beata María Ana Hospital of Madrid and referred from other collaborators centers and hospitals or self-referrals that know the research project due to the dissemination through social networks. The subjects included will be assessed by a neurologist expert in movement disorders ([name])) (Figure 1). All patients will be idiopathic PD patients diagnosed according to the UK Parkinson’s Disease Society Brain Bank criteria. The inclusion and exclusion criteria are shown in Table 1. During the protocol, changes in dopaminergic medication will be prohibited and, if necessary, will lead to the exclusion of the patient. The total daily dose of dopaminergic drugs will be recorded and controlled in the final analysis of the results.

To control the Wearing-off effect, a specific questionnaire will be applied both at the beginning and at the end of the study [23].

The data will be anonymized and will be recorded separately, being safeguarded in accordance with current European data protection laws. All data will be recorded and verified twice in a database designed for the study.

The study design will be a parallel, randomized and controlled experimental study. The patients included in the sample will be divided into two groups: Cognitive rehabilitation (experimental) and no therapy (control). The distribution will be random, but it will be ensured that there is an equitable number of subjects in each of the stages of the disease, being matched by their score in HY. The randomization of the sample will be done through the website: http://www.randomization.com/ (accessed on 12 February 2020). The duration of the study will be 18 months.

The sample will be composed of 46 patients randomly distributed in a 1:1 ratio (Figure 1). To calculate the sample size, we used the GRANMO calculator. Accepting an alpha risk of 0.05 and a beta risk of 0.2 in a one-sided contrast, 23 subjects are required to detect a difference equal to 12 points in the Biodex objective stability limits test assessment (Biodex, Version 1.08, Biodex, Inc., Shirley, NY, USA). The standard deviation in the stability limits test obtained in our sample from the NeuroMOD project was 16.16. Considering a 15% loss, it will be necessary to reach a sample of 26 patients in each group.

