### 2.4. Data Analyses

The SPSS software package (version 25.00; SPSS Inc., Chicago, IL, USA; IBM, New York, NY, USA) will be used by a blinded statistician for statistical analysis of the data. Demographic and clinical variables will be presented as mean and standard deviation. A 95% confidence interval (CI) will be taken, considering statistically significant all those values that had a *p* < 0.05. Parametric statistical tests will be used for hypothesis testing (*n* > 30). To show the differences in the variables, a 2 × 2 analysis of variance (ANOVA) of repeated measures will be carried out, taking time and group as factors, being the control and experimental groups and the pretreatment and posttreatment time measures. If significant differences are found in any of the interactions, a post hoc analysis with Bonferroni correction will be performed. The effect sizes will be calculated using Cohen’s d, classifying them into small (d between 0.20 and 0.49), medium (d between 0.50 and 0.79), or large (d greater than 0.80) following Cohen’s method.

Possible confounders or mediating variables will be included as covariates in the analysis.

For the rest of the variables, a Pearson correlation or linear regression will be carried out with the motor and balance variables. The low correlation will be that with values between 0.2 and 0.39; the correlation will be considered moderate when the value goes from 0.40 to 0.79; and high when the correlation value is greater than 0.80.

For the EEG entropy analysis, nonparametric Kruskal–Wallis (KW) tests will be performed to compare the distributions, the Mann–Whitney U test to evaluate the difference between the median values, and the Wilcoxon rank sum test for measure pre/post intervention changes, with a significance level of 0.05 and the alternative hypothesis of unequal values. Therefore, small *p*-values will suggest significant differences between populations.

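### The Discussion promises markers of who benefits from the intervention, but the stated correlations or regressions with balance include no group-by-marker term and cannot show this

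*Protocol article*

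**What the plan says.** Section 3 (Discussion) of the protocol article states without qualification: "All the clinical variables assessed will allow one to identify markers that predict a better outcome of the cognitive intervention on balance rehabilitation". It adds that this information will be used to "adjust the intervention to specific profiles of patients with PD who will benefit the most".

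Section 2.4 (Data Analyses) states three things that bear on this:

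- The main model is a repeated-measures ANOVA with two factors, time and group. No marker is among them.
- Confounding or mediating variables enter as covariates. No product with group is mentioned.
- "For the rest of the variables, a Pearson correlation or linear regression will be carried out with the motor and balance variables". The correlations are then graded by fixed cut-offs for their size.

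The text does not say whether these associations are computed over both arms or within one, or on baseline, final or change values. The article contains no test of whether the treatment effect differs by marker.

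**The concern.** A marker of who benefits is a variable along which the experimental-minus-control difference changes. Finding one requires comparing the marker–balance relation between arms. A Pearson correlation with balance does not do that: it also picks up any variable that goes with better or worse balance regardless of treatment, that is, a prognostic variable. Restricting it to the experimental arm does not help, because the control slope is then never seen.

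Prognostic relations are to be expected in this trial. The Introduction argues that attention and executive function are related to balance in Parkinson's disease generally, and these are among the domains that the cognitive battery measures. A correlation between such a score and balance would be unsurprising without any treatment effect at all.

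At stake is a published statement about which patients to treat that rests on an association saying nothing about treatment benefit.

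**Working it through.** **Inputs from section 2.1.** One-sided α = 0.05; β = 0.2, that is, 80% power; a target difference of 12 points with 23 per arm; SD 16.16, taken from the investigators' own earlier project; 46 patients in all, allocated 1:1. The section also gives 26 per group after allowing for losses, so 23 per arm is used below, with 20 to 26 as a range. The documents give no figure for a marker analysis. Marker strength, the marker split and the size of any marker shift are therefore assumptions.

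**1. The plan's own figure.** n per arm = 2 × (1.645 + 0.842)² × (16.16/12)² = 2 × 6.18 × 1.8135 = 22.4, rounded up to 23. This reproduces the stated number; power at 23 per arm is 80.9%.

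**2. Does the correlation separate prognostic from predictive?** 20,000 trials were simulated with 23 per arm, a treatment effect of 12/16.16 = 0.74 SD, and a marker equally correlated with balance in both arms, so that there is no effect modification. Share of trials with p < 0.05:

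| Marker–balance correlation | Pooled correlation | Experimental arm only | Group-by-marker interaction |
|---|---|---|---|
| 0.3 | 47% | 28% | 5.0% |
| 0.5 | 92% | 71% | 5.3% |

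For a genuinely predictive marker (correlation 0.5 in the experimental arm, 0 in control), the pooled correlation is significant in 36% of trials and the interaction in 40%. The pooled correlation thus flags a moderate prognostic marker (47%) more often than a real predictive one (36%).

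**3. What could the right test detect?** Assume a binary marker split 50:50, so four cells of 11.5, SD 16.16 and no baseline adjustment.

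- Main-effect SE = 16.16 × √(2/23) = 4.77.
- Interaction SE = 16.16 × √(4/11.5) = 9.53, twice as large.
- Interaction detectable with 80% power: (1.645 + 0.842) × 9.53 = 23.7 points one-sided; (1.960 + 0.842) × 9.53 = 26.7 points two-sided.
- Against the 12-point target: 23.7/12 = 1.98 and 26.7/12 = 2.2.
- Power for a 12-point interaction: 35% one-sided, 24% two-sided.
- From 20 to 26 per arm: detectable interaction 25.4 to 22.3 points one-sided and 28.6 to 25.1 two-sided; two-sided power 22% to 27%.

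**4. Effect of baseline adjustment.** If baseline and final balance correlate at ρ, both SEs shrink by √(1 − ρ²), so their ratio stays at 2. The documents give no ρ. At ρ = 0.5 (factor 0.866) the detectable interaction is 20.5 one-sided or 23.1 two-sided. At ρ = 0.7 (factor 0.714) it is 16.9 or 19.1. To reach 12 points, ρ would have to be √(1 − (12/23.7)²) = 0.86 one-sided or √(1 − (12/26.7)²) = 0.89 two-sided.

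**5. Conditional case: change scores correlated over both arms.** Suppose treatment shifts balance by 0.74 SD and the other variable by an assumed amount, with no link within arms. The pooled correlation is then significant in 8.7%, 13.1% and 18.0% of trials for shifts of 0.5, 0.74 and 1.0 SD (mean r 0.09, 0.12 and 0.16). Within the experimental arm it stays at about 5%. For a baseline marker unrelated to balance, the pooled rate is 5.1%, which is nominal.

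**The case against.** Four arguments can be made for the plan.

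- **Section 2.4 never says that the correlations are meant to find markers of benefit**, and the Discussion names no analysis. The correlations could simply describe how cognition and balance relate. This is fair. But they are then the only stated analysis that could carry the claim, and otherwise the claim has none.
- **Linear regression can include a group-by-marker term, and a full protocol or analysis plan may specify one.** This stands as far as it goes: a reader might infer that the plan has fixed a regression without an interaction, and the text does not say that. The point here is not the missing detail. It is an unhedged promise set beside a method that, as written, does not deliver it. An interaction term in an unseen document would correct the method but, at this sample size, not support the promise.
- **Pooling.** A reader might infer that the plan pools the arms and so manufactures spurious markers. The documents do not support that. They say neither that arms are pooled nor that change scores are used. Variables used to select patients before treatment are baseline variables, and for these randomisation keeps the pooled false-positive rate at about 5%. The inflation in step 5 is a conditional caution about change-on-change associations only.
- **The sentence is an aspiration in the Discussion.** The stated aims and main hypothesis contain no marker objective. This stands, and it limits the severity.

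**Conclusion.** The point holds as a mismatch between claim and method, and it is minor. A Pearson correlation with balance cannot identify who benefits, whether computed in both arms or one. A regression can do so only with a group-by-marker term, which is not stated. Under the assumptions of a 50:50 binary marker, SD 16.16, 23 per arm and no baseline adjustment, the interaction would have to be about 24 points (one-sided) or 27 points (two-sided) for 80% power, about twice the effect the trial is sized for. Baseline adjustment narrows this, but reaches 12 points only at a baseline–final correlation near 0.86 to 0.89. The correct test is therefore exploratory in this trial.

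It would be too strong to conclude that the trial's main results are at risk. The comparison of the two groups on balance, and the secondary outcome comparisons, do not depend on this analysis.

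**What to change.** 1. For any statement about who benefits, model post-intervention balance on baseline balance, group, baseline marker and group × marker. Do this for a short list of baseline markers named in advance, label it exploratory, and report the interaction estimate with its confidence interval.
2. In the Discussion, say that the assessed variables *may generate hypotheses about* markers of response, and drop the statement that the results will be used to tailor the intervention to patient profiles.
3. If change in one measure is related to change in balance using both arms, include group in the model.
4. Correlations that only describe how cognition and balance relate can stay, presented as such.

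The cost is analysis wording and a less ambitious exploratory conclusion. Design, sample size and data collection are unchanged.

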## 4. Conclusions

Cognitive therapy through neurorehabilitation platforms opens up the possibility of new rehabilitation strategies for the prevention of falls in PD, reducing morbidity, and saving costs for the health system.

## Figures and Tables

**Figure 1 medicina-57-00314-f001:**
[figure not shown]
Standard Protocol Items: Recommended Items for Interventional Trials (SPIRIT) study flow chart.

**Figure 2 medicina-57-00314-f002:**
[figure not shown]
Schematic representation of the study experimental procedures.

**Table 1 medicina-57-00314-t001:** Inclusion and exclusion criteria.

Inclusion Criteria	Exclusion Criteria
Idiopathic Parkinson’s disease (diagnosed according to the UK Parkinson’s Disease Society Brain Bank criteria). Older than 18. Stage < III Hoehn–Yahr with no obvious motor fluctuations.	Visual-perceptual difficulties. Peripheral sensory disturbances due to polyneuropathy. Cerebellar alterations. Impossibility to operate a computer due to motor impairment Severe cognitive impairment (MoCA < 24). Moderate or severe active depression (BDI > 14). Dependence (mRS > 3). Dopaminergic medication changes in the last 30 days. Structural changes MRI Severe comorbidity (cancer, severe COPD, etc.). Atypical data for idiopathic PD.

## Data Availability

The data presented in this study will be available on request from the corresponding author.
